#### Sample size calculation.

The sample size calculation was based on the study by Lichen et al. (2021), which reported a difference of 0.98 on a Likert scale (ranging from 1 to 6) when assessing patient experience before and after the comfort cart intervention [3]. Considering a power of 90% and a significance level of 5%, 132 patients will be required in each group (pre- and post-intervention), totaling 264 participants.

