**Table pone.0332773.t001:** 

Questions adapted from Lichen et al. (2021)			
* Question *		* Response options *	
*During your stay in the ED, what was your average comfort level?*		Very comfortable; Comfortable; Somewhat comfortable; Somewhat uncomfortable; Uncomfortable; Very uncomfortable	
*As a person in the emergency department, do you feel you were offered care specific to your individual needs (I.e. needs related to communication, hearing, vision, etc.)?*		Strongly agree; Somewhat agree; Neither agree nor disagree; Somewhat disagree; Strongly disagree	
Additional questions in the post-implementation phase			
*Did you use any of the items or services offered in the Geriatric Cart?*		Yes; No	
*Knowing that these items or services were available, even if I did not use them, made me feel more comfortable*		Strongly agree; Somewhat agree; Neither agree nor disagree; Somewhat disagree; Strongly disagree	
*The items I requested from the comfort cart made me feel more comfortable during my visit today*		Strongly agree; Somewhat agree; Neither agree nor disagree; Somewhat disagree; Strongly disagree	
*Having the comfort cart available improved my overall experience today*		Strongly agree; Somewhat agree; Neither agree nor disagree; Somewhat disagree; Strongly disagree	
*Having the comfort cart gave me more independence during my visit today*		Strongly agree; Somewhat agree; Neither agree nor disagree; Somewhat disagree; Strongly disagree	

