### Data management and statistical analysis

All study data will be collected and managed using Research Electronic Data Capture (REDCap) [30], a secure web-based application. Research assistants will use tablets with online access to the REDCap database for direct data entry and informed consent procedures.

For the primary objective evaluating the impact of the comfort menu and cart on the experience of older patients we will use the questionnaire adapted from Lichen et al. (2021) and McCusker et al. (2018). For the secondary objectives evaluating the impact of a comfort menu and cart on the experience of medical and multidisciplinary staff involved in caring for older patients treated in the ED, we will use the the questionnaire adapted from Lichen et al. (2021).

Data analysis will be performed using Stata version 17 (StataCorp, College Station, TX). All statistical tests will be two-tailed with an alpha error of 0.05. Numerical variables will be reported as means and standard deviations or medians and interquartile ranges (IQR) depending on their distribution, which will be assessed visually and using the D’Agostino-Pearson test for normality. Categorical variables will be described as absolute counts and proportions. Numerical variables will be compared using Student’s t-test or ANOVA for normal distributions and Wilcoxon or Kruskal-Wallis tests for non-normal distributions. As appropriate, categorical variables will be compared using the chi-square test or Fisher’s exact test. Analyses will be adjusted to account for potential confounding variables, such as baseline frailty, cognitive impairment, and clinical severity. Missing data will be handled though mixed effects model.

All relevant data from this study will be made available upon study completion.

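### The 132 patients per group do not follow from the cited 0.98-point difference at any realistic SD; the mismatch is conservative, but the basis needs restating

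*Protocol article*

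**What the plan says.** The Sample size calculation section of the protocol article takes one effect from a prior comfort cart study, a "difference of 0.98 on a Likert scale (ranging from 1 to 6) when assessing patient experience before and after the comfort cart intervention". It then gives the power, the significance level and the result: "Considering a power of 90% and a significance level of 5%, 132 patients will be required in each group (pre- and post-intervention", 264 patients in total.

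The section gives no SD, standardised effect, test or allowance for attrition. It does not say in so many words that 0.98 is the difference to be detected, but it prints no other effect.

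The Data management and statistical analysis section settles the sidedness: "All statistical tests will be two-tailed with an alpha error of 0.05". The same section plans a t-test or a Wilcoxon test for numerical variables, depending on their distribution.

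In the patient questionnaire, the average comfort item is the one with six ordered answers: "Very comfortable; Comfortable; Somewhat comfortable; Somewhat uncomfortable; Uncomfortable; Very uncomfortable". It therefore matches the 1 to 6 scale named in the sample size section.

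**The concern.** An unstated SD alone would be ordinary condensation in a journal article. Here the scale range is printed as well, and a bounded scale bounds the SD. The printed difference, power, significance level and group size together push the SD to that bound. It could be reached only if practically every patient gave one of the two extreme answers.

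What is at stake is how the result will be read. The paragraph tells readers that the study is sized for a difference of about one scale point. If the SD is between 1.0 and 1.5, the study has 90% power for 0.40 to 0.60 points, so a significant result could be about half the effect named as the basis. The difference the study was really sized for is not disclosed. If 132 was meant as the total, recruitment is twice what was calculated.

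**Working it through.** **Inputs from the protocol article**
- Difference δ = 0.98 points, scale 1 to 6, power 90%, 132 per group in two independent groups (Sample size calculation).
- Two-sided 5% (Data management and statistical analysis).
- SD and inflation are not stated; the values below are assumptions.

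**1. Trying to reproduce 132**

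Normal approximation: n per group = 2(z₀.₉₇₅ + z₀.₉₀)² × (SD/δ)², with (1.960 + 1.2816)² = 10.507.

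Solved for the SD: SD = 0.98 × √(132 / (2 × 10.507)) = 2.456. The t-test calculation (noncentral t) gives 2.447.

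**2. The largest SD the scale allows**

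For a mean m on a 1 to 6 scale, the largest SD is √((m − 1)(6 − m)).
- One group, m = 3.5: √(2.5 × 2.5) = 2.50.
- Two groups 0.98 apart and centred, m = 3.01 and 3.99: √(2.01 × 2.99) = 2.4515. Any off-centre placement gives a smaller pooled value.

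The normal-approximation SD (2.456) lies just above this limit and the t-test SD (2.447) just below it. For comparison, answers spread evenly over all six options have an SD of √(35/12) = 1.71, which needs 65 per group by the t-test.

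**3. What 0.98 points needs, and what 132 per group delivers**

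The detectable difference at 90% power is SD × 3.2415 × √(2/132) = 0.399 × SD (0.4005 × SD by the t-test).

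| Assumed SD | n per group for 0.98 (t-test) | Power for 0.98 with 132 per group | Difference detectable at 90% power with 132 per group |
|---|---|---|---|
| 1.0 | 23 | over 99.9% | 0.40 |
| 1.25 | 36 | over 99.9% | 0.50 |
| 1.5 | 51 | over 99.9% | 0.60 |
| 2.0 | 89 | 97.8% | 0.80 |

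The normal approximation gives 22, 35, 50 and 88 per group.

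**4. Other routes to 132 for a 0.98-point difference (none is documented)**

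| Route | SD needed |
|---|---|
| One-sided 5% | 2.72 (impossible on this scale) |
| 10% attrition, 118.8 evaluable per group | 2.33 |
| 20% attrition, 105.6 evaluable per group | 2.20 |
| 20% attrition and Wilcoxon efficiency 0.864 | 2.04 |
| 30% attrition, 92.4 evaluable per group | 2.05 |
| 132 as the total, 66 per group | 1.74 |

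**5. A standardised difference of 0.40**

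The normal approximation gives 2 × 10.507 / 0.16 = 131.3, rounded up to 132. The t-test gives 132.3, hence 133. The match is close but depends on the method.

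**The case against.** The strongest reply is that an article condenses a fuller protocol. The SD, the test and an attrition allowance may be stated there, and the article says only that the calculation was based on the prior study. An inflation, a deliberately smaller target, or a total printed as a per-group number could each explain 132.

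Part of this stands. The document does not show where 132 came from. A reader might infer that the planning basis is wrong, or that it must have been a standardised difference of 0.40. Neither is supported: 0.40 gives 132 only under the normal approximation, and the other routes cannot be excluded.

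It does not rescue the paragraph as printed. The text says that 132 are required at the stated power and significance level and mentions no inflation. The attrition routes tried still need an SD of 2.04 or more, well above the 1.71 of evenly spread answers.

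A second reply is that the discrepancy is on the safe side, and this stands in full. For any feasible SD, 132 per group gives at least about 90% power for 0.98 points. A reader might take an irreproducible sample size to mean an underpowered study; the figures show the opposite for the cited difference. Interpretation will also rest on the estimate and its confidence interval, which limits the harm.

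**Conclusion.** The concern holds as a defect in the stated link between effect, power and sample size. Taken as printed, 0.98 points, 90% power and two-sided 5% give 132 per group only at an SD of about 2.45, essentially the limit of 2.4515 for two centred groups that far apart (2.50 is the limit for one group). At assumed SDs of 1.0 to 2.0 the cited difference needs 23 to 89 per group, and 132 per group has 90% power for 0.40 to 0.80 points.

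The figures rest on a comparison of two independent means without inflation and on assumed SDs, since the document gives none. The remark that the detectable difference is about half the cited one holds for SDs of 1.0 to 1.5, not for 2.0.

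This should be corrected, but it is not critical. The study is not underpowered for 0.98 points, and the source of 132 is unknown rather than shown to be mistaken.

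**What to change.** Keep the 264 patients and rewrite the Sample size calculation paragraph:
- Remove the statement that a 0.98-point difference requires 132 per group.
- State that 132 per group gives 90% power at two-sided 5% for a standardised difference of about 0.40. If this is translated into scale points, name the SD used.
- Give the target difference, the SD and its source, the test and any inflation actually used, and reconcile them with 0.98. Say whether 132 was meant as a total.
- Do not present 0.40 as the basis of the calculation unless the sponsor confirms that it was; otherwise the text becomes a rationale fitted to the number afterwards.

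The cost is one paragraph and a look at the calculation file. Recruitment numbers do not change, and the start planned for April 2026 need not be delayed.

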### Study setting

The study will be conducted in the ED of HSL, a tertiary philanthropic hospital in São Paulo, Brazil [8]. The ED receives over 80,000 patients annually, providing continuous care for private and insured patients seeking emergency treatment. Patients undergo initial triage using a modified Manchester Triage System to classify risk and prioritize care [9]. In 2017, HSL inaugurated the Specialized Geriatric Emergency Department (ProAGE), which offers additional geriatric risk assessment for patients over 70 [10]. In 2019, the ED received the Geriatric Emergency Department Accreditation (GEDA), marking the first hospital in the Southern Hemisphere to achieve this recognition [11].

The ED has 14 examination rooms, 3 procedure rooms, 15 chairs for rapid medication administration, and 22 private rooms where patients requiring complex care due to age, mobility limitations, frailty, behavioral changes, or continuous vital sign monitoring are accommodated. Between January 2023 and June 2024, an estimated 9,608 patients over 65 years old were treated in these private rooms, averaging 533 patients per month.

### Data collection

#### Recruitment.

A trained research assistant will recruit participants in the ED, working 25 hours per week (five 5-hour shifts between 10:00 am and 10:00 pm) over six months (three months pre-intervention, from April 2026 to June 2026, and three months post-intervention, from July 2026 to September 2026). The assistant will conduct active searches for potential participants. Eligible patients will be invited to provide informed consent.

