#### Initial interview.

The interview will start with a questionnaire adapted from Lichen et al. (2021) and McCusker et al. (2018) [2,3].

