#### Follow-up interview.

A second research assistant, blinded to the initial assessment and ED care details, will conduct a phone interview 30 days (± 2 days) post-initial assessment. This interview will assess the following:

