## Discussion

Our study focuses on implementing and evaluating a comfort menu and cart, a non-pharmacological, innovative intervention designed to enhance the experience of older adults in the ED. This approach aligns with international guidelines emphasizing the importance of creating a supportive and age-friendly ED environment. By providing older patients access to items that promote comfort, communication, and engagement, we aim to improve their overall experience, potentially leading to better clinical outcomes.

While previous studies have explored similar interventions in other acute care settings, our study will provide valuable evidence specific to the ED context. Furthermore, our study will be the first to assess the impact of this intervention on a wide range of patient-centered outcomes measured up to 30 days after the initial ED visit. This longitudinal perspective will provide a more comprehensive understanding of the potential benefits of the intervention. Our study will also advance the growing body of literature on non-pharmacological interventions for older adults in acute care settings. By demonstrating the feasibility and effectiveness of a relatively simple and low-cost intervention, our study can encourage wider adoption of similar approaches in EDs and other healthcare settings.

Our study has limitations that should be acknowledged. Firstly, it will be conducted in a single tertiary philanthropic hospital in Brazil, which may limit the generalizability of the findings to other ED settings, particularly those with different resource availability or patient populations. Secondly, while allowing for a comparison of outcomes before and after the intervention, the before-and-after design, is not as robust as a randomized controlled trial in establishing causality. Thirdly, the reliance on patient and staff self-reported data for assessing experience and comfort may introduce some information bias. However, we will use validated questionnaires and scales to mitigate this potential limitation. Finally, the 30-day follow-up period may not be sufficient to understand potential longer-term effects of the intervention. Future studies with longer follow-up periods are warranted.

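### The primary experience questionnaires are collected in an ED interview by an assistant who must know the phase, and assessor blinding is stated only for the exploratory day-30 call

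*Protocol article*

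**What the plan says.** All references are to the protocol article.

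- **Recruitment.** "A trained research assistant will recruit participants in the ED". The phases are fixed by date: "three months pre-intervention, from April 2026 to June 2026, and three months post-intervention, from July 2026 to September 2026".
- **Initial interview.** The interview begins with the two adapted experience questionnaires. The section does not say who conducts it. The first questionnaire has two items common to both phases, including "During your stay in the ED, what was your average comfort level", which has six ordered answers. The second has eight items, each classed as problem or no problem. Further questions about the cart are asked only in the post-implementation phase.
- **Data management and statistical analysis.** Both questionnaires are assigned to the primary objective. "Research assistants will use tablets with online access to the REDCap database for direct data entry and informed consent procedures". Analyses are to be adjusted for confounders such as frailty, cognitive impairment and clinical severity.
- **Follow-up interview.** "A second research assistant, blinded to the initial assessment and ED care details, will conduct a phone interview". The Secondary objectives section labels the 30-day outcomes exploratory.
- **Ethics and dissemination.** The consent form withholds details of the intervention, to limit information bias on the participants' side.
- **Discussion.** Among the limitations, "the reliance on patient and staff self-reported data for assessing experience and comfort may introduce some information bias". The answer offered is the use of validated instruments. The interviewer is not mentioned.

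**The concern.** The primary outcome is a set of subjective answers given in an interview. An interviewer who knows whether the cart is in place can influence such answers without intending to, through tone, through prompting, or in settling a hesitant reply between neighbouring options such as comfortable and somewhat comfortable. The protocol also says that it expects a positive result.

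Every pre-intervention interview would be taken knowing there is no cart, and every post-intervention interview knowing there is one. A change in interviewer behaviour would therefore be indistinguishable from the effect of the cart. The one stated assessor safeguard protects exploratory outcomes and leaves the primary outcome uncovered.

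**Working it through.** **Who takes the answers, and do they know the phase?**

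1. The Recruitment section describes one assistant working in the ED through both phases. The Follow-up interview section calls the telephone interviewer the second assistant. The data management section has research assistants entering data on tablets. Together these suggest that the recruiting assistant also conducts the initial interview. This is an inference; no sentence states it.
2. The next step does not depend on that inference. Phases are set by calendar, and the form contains cart questions in one phase only, so any person conducting the interview knows the phase.
3. The consent-form measure masks participants, not the interviewer. The Discussion names self-report only.
4. The planned adjustment uses patient characteristics. An interviewer shift is a function of phase alone, so no patient covariate can separate it from the phase effect.

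**How sensitive is the comparison? (comfort item only)**

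Inputs from the protocol: 132 per group, two-sided 5% test, 90% power, planned difference 0.98 on a 1 to 6 scale. No SD is stated.

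SD implied by the plan's own sample size:

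SD = 0.98 × √(132/2) / (1.960 + 1.282) = 0.98 × 8.124 / 3.242 ≈ 2.46.

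This is close to 2.5, the largest SD possible on a 1 to 6 scale (half the answers at each end), so smaller SDs are shown as well. They are assumptions.

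Formulas, with true effect zero and an average interviewer shift b:

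- SE = SD × √(2/132)
- P(significant) = Φ(b/SE − 1.96) + Φ(−b/SE − 1.96)

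Worked example, SD 1.0 and b = 0.25: SE = 0.123; b/SE = 2.03; P = Φ(0.07) + Φ(−3.99) ≈ 0.53.

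| SD | SE | Smallest significant difference | b = 0.10 | b = 0.15 | b = 0.25 |
|---|---|---|---|---|---|
| 1.0 | 0.123 | 0.24 | 13% | 23% | 53% |
| 1.2 | 0.148 | 0.29 | 10% | 17% | 39% |
| 1.5 | 0.185 | 0.36 | 8% | 13% | 27% |
| 2.46 | 0.302 | 0.59 | 6% | 8% | 13% |

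The nominal rate is 5%. A shift of 0.25 corresponds to moving one respondent in four by one category. The values of b are also assumptions, since the protocol gives no information on interviewer effects.

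**The case against.** Several points on the other side are fair.

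- **Phase cannot be concealed.** In a calendar-based before-and-after study, nobody working in the ED can be blinded to phase, whereas a separate telephone caller can be kept from the ED care details. The two blinding arrangements therefore do not contradict each other. This stands, and it is why the remedy is less interviewer influence, not blinding.
- **A condensed article may omit the interview script.** The assistant is described as trained, six months are scheduled for hiring and training, and the items have fixed wording and closed options. This stands in part: the absence of a script from the article is not itself a fault. It does not answer the point that blinding is stated for exploratory outcomes and that the limitations leave the interviewer out.
- **The limitation is partly conceded.** The Discussion accepts that the design is weaker than a randomised trial and that self-report may bring information bias. Interviewer bias is a related matter, but validated instruments do not protect against the person administering them.
- **The illustration is assumed and partial.** Any systematic shift inflates the rejection rate in this formula, and the calculation covers one item of ten. This stands.

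A reader might infer that the protocol has the recruiting assistant take the answers orally, or that the primary claim rests on the six-category comfort rating alone. The documents support neither as fact. The interviewer's identity and the oral mode are inferred, and the primary objective is assigned to both questionnaires. The Patient and public involvement section ties the primary experience measures to the eight-item one.

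**Conclusion.** The concern holds as a vulnerability of the design, not as a demonstrated bias. The primary experience answers are collected in an interview by someone who must know the phase. Assessor blinding is stated only for the exploratory day-30 call. An interviewer shift would be fully confounded with phase and cannot be adjusted away.

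Its size is unknown. For the comfort item, an assumed 0.25-point shift with no true effect would be significant in 27% to 53% of trials over SDs of 1.5 to 1.0, and in about 13% at an SD of 2.46. These figures rest on the assumed shift and SD and do not describe the eight problem/no-problem items. A reader might take them as the trial's actual false-positive rate; the documents give no basis for that. The change is worth making before enrolment, because collection mode cannot be made uniform across phases once pre-intervention interviews have begun.

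**What to change.** In both phases:

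1. Let the patient, or the companion who responds, mark the ten common experience items (two from the first questionnaire, eight from the second) on the study tablet or a printed response card. The assistant does not see the answers, and the items are completed before any cart question is shown.
2. Where that is not possible, the assistant reads each question and its options verbatim, without prompts.
3. Offer the same reading aids for completing the form in both phases. The cart supplies reading glasses and a magnifying glass only after implementation, so without this the ability to self-mark could itself change with phase.
4. Record the mode (self-marked or read aloud) and report it by phase, descriptively.
5. Keep all respondents in the primary comparison. Do not repeat it in self-markers only, because that subset would be selected on something the intervention can alter.
6. Name interviewer bias among the limitations in the Discussion.

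Cost: one self-entry screen and one mode field in REDCap, a response card, and reading aids for form completion in the pre-intervention phase. Staff and tablets are unchanged. Some respondents will still need the items read aloud, and a few more items may be left blank.
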